**Table 1 Tab1:**
[figure not shown]
Time of data collection during the randomised control trial and process evaluation

^*^*SPR* Swedish Pregnancy Register

^*^*MHCs* Maternal health clinics

The questionnaire will be completed digitally, manually on paper, or via telephone by interpreter amongst women who are illiterate or prefer this method. The printed paper questionnaire has been translated into the nine most common languages spoken by immigrants in Sweden. Participants will chose to receive follow-up text messages, e-mails or paper questionnaires at six and 12 month after the post-partum visit. Those who answered via telephone will be recalled. Several reminders/recalls will be performed.

The organizational outcomes including the MHCs’ and midwives’ readiness, motivation, competence and confidence will be measured through project documentation and a questionnaire (Table 1).

### Power analysis and randomisation

The intraclass correlation coefficient (ICC) was set to 0.05 in the power analysis, equivalent to an observed ICC in a similar study [66]. To detect an anticipated 15 percentage point increase in choosing an effective contraceptive method (SARC/LARC) with 90% power at an α = 0.05 (i.e. the probability of rejecting a true null hypothesis), we needed to include at least 30 MHCs, each contributing an average of 100 participants (pregnant women). However, 28 (out of 52) agreed to participate in the study. This implies a statistical power of about 88% which was considered sufficient. The sample size calculations were performed using Stata version 17.0 [67]. No power calculations were performed for secondary outcomes.

The randomisation procedure followed a blocked cluster design. The MHCs (clusters) were first assigned to groups (blocks) based on their regional affiliation and size (number of visits by immigrant mothers in the past year), resulting in two blocks for Jonkoping and Stockholm and three blocks for Vastra Gotaland. Intervention and control status was then randomly assigned to clusters within each block.

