### Statistical analysis

The analysis population will consist of all women in the cRCT. Our primary goal is to estimate the effect of the QIC on choosing an effective contraceptive method using logistic regression analysis, relying on the randomization scheme to retrieve a causal estimate. We will also investigate whether the intervention effect varies by sociodemographic variables and reproductive history.

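### Clinics were randomised within blocks of region and immigrant-visit volume, but the stated primary model and covariate list do not name the block; adding it is nearly free and, if the blocks are prognostic, restores the test level and some power.

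*Protocol article*

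**What the plan says.** In the protocol article, the section Power analysis and randomisation describes a blocked cluster design. Clinics were grouped by region and by the past year's number of visits from immigrant mothers, "resulting in two blocks for Jonkoping and Stockholm and three blocks for Vastra Gotaland". Then "Intervention and control status was then randomly assigned to clusters within each block". Block sizes and the allocation ratio are not given.

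The section Statistical analysis says the effect will be estimated "using logistic regression analysis, relying on the randomization scheme to retrieve a causal estimate". It names no block term and no cluster term. The abstract (Methods) adds a multivariate analysis controlling for age, sociodemographic characteristics and reproductive history. Region, clinic size and block are not in that list.

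The power calculation uses an ICC of 0.05 and a 15 percentage point increase. It states that "we needed to include at least 30 MHCs, each contributing an average of 100 participants (pregnant women"), and says of the 28 clinics obtained: "This implies a statistical power of about 88% which was considered sufficient".

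**The concern.** The plan rests its inference on the randomisation scheme, and that scheme is randomisation within blocks. The article names the model family and some covariates, but not the two factors on which the allocation was balanced.

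Blocking removes between-block differences from the treatment comparison. A model without a block term still counts those differences as noise. The interval is then wider than it should be, the true test level falls below its nominal 5%, and some power is lost. With only 28 clinics, and between-clinic variation supplying most of the variance, this can matter.

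There is some reason to expect the blocks to be prognostic. The Introduction reports that immigrant women are less likely to use reliable contraception in good time after birth, and the blocks use immigrant-visit volume. The process evaluation also expects delivery to vary between county councils. The trial fell two clinics short of its target, so power that can be recovered by a model term is worth having.

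**Working it through.** **Inputs from the article:** 28 clinics; an average of 100 women per clinic; ICC 0.05; a difference of 15 points; α = 0.05.

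**Assumptions (not in the article):** two-sided test; control proportion 42.5%, so 57.5% under intervention; equal clinic sizes; 14 clinics per arm; seven blocks (2 + 2 + 3) of four, with two clinics per arm in each; and a share *s* of between-clinic variance that lies between blocks.

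**Step 1: reproduce the stated power.** The design effect is 1 + 99 × 0.05 = 5.95. With 14 clinics per arm, SE = √(2 × 0.425 × 0.575 × 5.95 / 1400) = 0.0456, and 0.15 / 0.0456 = 3.29. A noncentral t with 26 df gives 88.6%. With 15 per arm (28 df), power is 90.8%. For control proportions from 35% to 50%, 15 clinics per arm are needed for 90%, and 14 per arm give 88.6% to 89.3%. The stated 30 clinics and about 88% are therefore reproduced closely, with no credit taken for blocking.

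**Step 2: the standard error with and without blocks.** The variance of one clinic's proportion is p(1−p)[ICC + (1−ICC)/100] = 0.2444 × (0.05 + 0.0095). The difference between two means of 14 clinics multiplies this by 2/14 = 1/7.

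- Under blocked 1:1 allocation the block component cancels. The true variance of the difference is 0.2444 × [0.05(1−s) + 0.0095] / 7. A model with blocks estimates this quantity.
- Without blocks, the residual sum of squares pools 6 between-block df with 20 within-block df. Write V_b for the between-block variance and V_w for the within-block variance of a clinic proportion. The expected mean square is [6(V_w + 4V_b) + 20V_w] / 26 = V_w + (24/26)V_b. The estimated variance is then about 0.2444 × [0.05(1−s) + 0.0095 + 0.05s × 24/26] / 7.

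| s | SE with blocks (correct) | SE without blocks | Ratio |
|---|---|---|---|
| 10% | 0.0436 | 0.0454 | 0.96 |
| 30% | 0.0394 | 0.0451 | 0.87 |
| 50% | 0.0347 | 0.0448 | 0.77 |

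The estimated difference is the same in both models; only its reported uncertainty changes.

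**Step 3: test level and power.** Simulation of this set-up (20,000 runs per scenario) compared a clinic-level t test without blocks (26 df) with one that includes blocks (28 − 7 − 1 = 20 df).

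| s | True level without blocks | Power without blocks | Power with blocks |
|---|---|---|---|
| 10% | 4.3% | 89.0% | 89.7% |
| 30% | 2.8% | 91.4% | 94.8% |
| 50% | 1.5% | 93.5% | 98.3% |

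With blocks the level stays at about 5% throughout.

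**Step 4: the price if blocks explain nothing.** At s = 0 both tests hold their level. The noncentral t gives 88.6% with 26 df and 87.9% with 20 df, a loss of 0.7 points. A separate simulation with a mean proportion of 50% gives 88.0% v 87.1%, a loss of 0.9. The cost is about 1 point.

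**The case against.** The strongest objection is that this is silence and not a choice. The statistical section is three sentences in a condensed article. It nowhere says that blocks will be left out, reliance on the randomisation scheme is compatible with conditioning on the strata, and a fuller plan may well include them. This stands in part. A reader might infer that the plan discards the blocks, and the text does not support that. It supports only that the article names a model and covariates, and that the block and its factors are not among them.

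Three other stronger readings also fail:

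- **That the analysis as written is conservative.** The conservatism arises only in a cluster-adjusted analysis, and the section names no cluster adjustment. A plain logistic regression that ignored clinics would err in the opposite direction, with a type I error of about 19% to 43% when blocks explain 75% down to 0% of between-clinic variance. That is a separate and larger question. Handling clustering would still leave this one open.
- **That blocks would lift power from about 89% to about 95%.** This sets a model without blocks at a zero share against a model with blocks at a 30% share. Blocked allocation already removes block variance from the comparison, so power without the term also rises with the share. Like for like, the gain is 91.4% to 94.8% at 30%, and under 1 point at 10%.
- **That the stated 88% is wrong.** It takes no credit for blocking, and omitting blocks left power at or above about 88% in every scenario examined.

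It is also fair to object that the block share, the block sizes and the allocation ratio are all assumed. The block wording can be read as five blocks in place of seven. The size of the effect is therefore conditional; the remedy is the same either way.

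**Conclusion.** The point holds as an efficiency and calibration matter. The design is blocked, and neither the stated primary model nor the listed covariates name the block or its factors. If a cluster-adjusted analysis omits prognostic blocks, the standard error is too large by an amount that depends on how prognostic they are: negligible at a 10% share, material at 30% to 50%. The error is towards caution. It creates no bias in the estimated difference under balanced 1:1 allocation and no excess of false positives.

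The balance is lopsided. Including blocks costs about 1 power point at worst, and gains about 3.4 points at a 30% share and 4.8 at 50%, with the test level restored to about 5%. These figures rest on 28 equal clinics of 100, ICC 0.05, seven equal blocks of four with 1:1 allocation, a control proportion of 42.5% and the assumed shares. The unchanged estimate applies on the difference scale. If allocation were unequal across blocks, a block term would also guard against confounding of arm with region or size, but the article does not give the ratio.

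**What to change.** State in the primary analysis that randomisation block (or region and size stratum) enters as a fixed effect in a cluster-adjusted model, with a small-sample correction using clinics minus blocks minus 1 degrees of freedom. That is 28 − 7 − 1 = 20 if there are seven blocks, or 28 − 5 − 1 = 22 if there are five. State the number of blocks, their sizes and the allocation ratio in the same place. If the full protocol or analysis plan already does this, a cross-reference is enough.

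The cost is one sentence and one model term. Block membership is already known, so no new data are needed. The downside is up to 6 degrees of freedom, or about 1 power point if the blocks turn out not to be prognostic. The change should be fixed before outcome data are analysed by arm.

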### Statistical analysis

The analysis population will consist of all women in the cRCT. Our primary goal is to estimate the effect of the QIC on choosing an effective contraceptive method using logistic regression analysis, relying on the randomization scheme to retrieve a causal estimate. We will also investigate whether the intervention effect varies by sociodemographic variables and reproductive history.

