**Methods:**

This Quality Improvement Collaborative (QIC) on contraceptive services and use will combine a cluster randomized controlled trial (cRCT) with a process evaluation. The cRCT will be conducted at 28 maternal health clinics (MHCs) in Sweden, that are the clusters and unit of randomization, and include women attending regular post-partum visits within 16 weeks post birth. Utilizing the Breakthrough Series Collaborative model, the study’s intervention strategies include learning sessions, action periods, and workshops informed by joint learning, co-design, and evidence-based practices. The primary outcome, women’s choice of an effective contraceptive method within 16 weeks after giving birth, will be measured using the Swedish Pregnancy Register (SPR). Secondary outcomes regarding women’s experiences of contraceptive counselling, use and satisfaction of chosen contraceptive method will be evaluated using questionnaires completed by participating women at enrolment, 6 and 12 months post enrolment. The outcomes including readiness, motivation, competence and confidence will be measured through project documentation and questionnaires. The project’s primary outcome involving women’s choice of contraceptive method will be estimated by using a logistic regression analysis. A multivariate analysis will be performed to control for age, sociodemographic characteristics, and reproductive history. The process evaluation will be conducted using recordings from learning sessions, questionnaires aimed at participating midwives, intervention checklists and project documents.

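### The stated primary analysis, a logistic regression of all women, names nothing for clinic or randomisation block; run as written at the planning inputs, its nominal 5% test has a type I error of about 42%

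*Protocol article*

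**What the plan says.** **Design.** The Methods part of the abstract describes the 28 clinics as units "that are the clusters and unit of randomization". The section Power analysis and randomisation says that clinics were first grouped by region and size, and then: "Intervention and control status was then randomly assigned to clusters within each block".

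**Sample size.** The same section states: "The intraclass correlation coefficient (ICC) was set to 0.05 in the power analysis". It plans 30 clinics averaging 100 women each for a 15-point difference, "with 90% power at an α = 0.05", and reports about 88% power with the 28 clinics that joined.

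**Analysis.** The Statistical analysis section takes every woman in the trial as the analysis population and sets the primary aim as estimating the effect of the collaborative "using logistic regression analysis, relying on the randomization scheme to retrieve a causal estimate". The abstract says that the primary outcome "will be estimated by using a logistic regression analysis" and adds a multivariable analysis with covariates measured on the woman only. Neither place mentions a random effect, GEE, cluster-robust standard errors, a clinic-level analysis or a block term.

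**The concern.** The design and the stated analysis use different units. The sample size is inflated for correlation between women of the same clinic, but the analysis as described takes women as its units and names nothing that carries this correlation into the standard error.

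The reason given for the model does not close the gap. Random allocation justifies a causal reading of the point estimate. The precision of that estimate depends on how many units were allocated independently, and these are the 28 clinics, not the women.

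The validity of the primary test is at stake. A logistic regression that treats women as independent would attribute ordinary differences between clinics to the intervention, and its confidence interval would cover the true effect much less often than 95% of the time.

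**Working it through.** **Inputs from the document:** 28 clinics (30 planned), average cluster size m = 100, ICC = 0.05, difference 15 points, α = 0.05.

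**Assumed, because not stated:** a two-sided test; a baseline proportion (10% to 80% scanned); for the simulations, seven blocks of four clinics. The article can be read as two blocks in each of two regions plus three in the third, but it does not give the number of clinics per block.

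**Step 1. Does the plan's own power figure allow for clustering?**

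- Design effect: DE = 1 + (m − 1) × ICC = 1 + 99 × 0.05 = 5.95.
- Effective women per arm: 1500 / 5.95 = 252 with 30 clinics; 1400 / 5.95 = 235 with 28.
- At the least favourable baseline (42.5% against 57.5%), a t reference on clinics − 2 degrees of freedom gives power of 90.8% with 30 clinics and 88.6% with 28. A normal reference gives 92.3% and 90.5%.

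The stated 90% and about 88% are reproduced, closely with the t reference and within about 2.5 points with the normal one. Without the design effect, the 30-clinic design would have a standard error of √(2 × 0.425 × 0.575 / 1500) = 0.018. A 15-point difference would be more than 8 standard errors, and power would be practically 100%. The stated figures therefore depend on the clustering allowance.

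**Step 2. Type I error if the analysis ignores clinic.**

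- Standard errors are too small by √5.95 = 2.44.
- Type I error = 2 × [1 − Φ(1.96 / √DE)] = 2 × [1 − Φ(0.80)] = 0.42.
- Coverage of a nominal 95% interval is then about 58% (1 − 0.42).

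This formula does not depend on the baseline proportion. To show the scale at an assumed 50% baseline with 1400 women per arm: the naive standard error is √(0.5 / 1400) = 0.0189, so a difference of 1.96 × 0.0189 = 3.7 points would be declared significant. With clustering the threshold is 2.44 × 3.7 = 9.0 points.

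**Step 3. Check by simulation under no effect** (28 clinics, 6,000 trials per setting). The naive test rejected in 43% of trials at a proportion of 50% and in 41% at 30%. A t-test on the clinic proportions, with the same data, rejected in 4.9% and 4.8%.

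**Step 4. Sensitivity to assumptions that are not the plan's.**

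| Assumed setting | Naive type I error |
|---|---|
| Blocks explain 30% of clinic variance | 35–36% (simulation) |
| Blocks explain 50% of clinic variance | 29–30% (simulation) |
| 30 women per clinic, ICC 0.05 (DE = 1 + 29 × 0.05 = 2.45) | 21% (formula) |
| 100 women per clinic, ICC 0.02 (DE = 1 + 99 × 0.02 = 2.98) | 26% (formula) |

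Stratifying the naive test by block left these rates nearly unchanged (for example 35% with and without blocks at a 30% share). Block terms alone do not solve the problem; the clinic must be accounted for.

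**The case against.** The strongest reply is that the point rests on silence. Logistic regression names a family of models, and a random intercept, GEE or cluster-robust errors all fit within it. The text comes from a condensed article, the full protocol and SAP are not shown, and the variance method is often left to the SAP. The authors plainly knew about clustering, since they paid for it in the sample size, so they may simply have abbreviated the analysis.

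Much of this stands. A reader might infer that the investigators intend to ignore clustering, or that the trial will have a false-positive rate above 40%. The document supports neither. It never says that the model is unadjusted for clinic, and the remark about the randomisation scheme explains the causal reading of the estimate without making a claim about standard errors. The block layout, the baseline and the share of variance due to blocks in the simulations are also assumptions, so only the 42% rests on the plan's own inputs.

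The reply does not remove the mismatch. The article is not silent on the primary analysis: it fixes the population, the model, the covariates and the reason for trusting the result. A statistician who follows that text would obtain invalid inference under the ICC that the article itself assumes. In a cluster-randomised trial, accounting for the cluster decides whether the primary test is valid, so it is more than a technical detail. The choice among particular small-sample corrections is such a detail and can be left to the SAP.

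**Conclusion.** The point holds in conditional form. The stated primary analysis does not match the cluster randomisation or the sample-size assumption. If it is run as written at ICC 0.05 and 100 women per clinic, standard errors are about 2.4 times too small and the nominal 5% test has a type I error of about 42%. Under the assumed alternatives the rate is lower, about 29–36% if blocks explain 30–50% of clinic variance and 21% at 30 women per clinic, but it stays far above 5%. The point estimate is not in question. If an SAP already specifies a cluster-aware model, what remains is an inconsistency in the protocol text. If none does, the trial's main conclusion is at risk. Because the primary test depends on it, the text must be corrected or confirmed before analysis.

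**What to change.** Add one sentence to the Statistical analysis section, for example: *The primary analysis is a logistic regression that accounts for clinic, by a random intercept for MHC or by GEE or cluster-robust standard errors clustered on MHC, with a small-sample correction suited to 28 clusters, and includes the randomisation blocks as covariates.* One option should be chosen in advance, and the abstract's wording should agree with it. If the SAP already specifies such a model, align the protocol text with it.

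The correction matters because the information on the effect comes from few units: with seven blocks (assumed), an intercept, six block terms and one treatment term leave 28 − 8 = 20 between-clinic degrees of freedom. A t-test on the 28 clinic proportions would serve as a simple check.

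No additional data or participants are needed. Confidence intervals become wider than under the model as written, by a factor of about 2.4 at the planning inputs, but they are valid. The sample size has already allowed for this through its ICC.

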### Process evaluation

The process evaluation started during the planning phase of the cRCT. Chosen improvement activities tested during action periods within three evidence-based areas of change, as well as the process itself, will be evaluated (Fig. 2). The study will use both quantitative and qualitative research methods to evaluate the QIC initiative in-depth and aims to discover which actions were carried out, what worked where, and how and why (or why not) an impact occurred.

**Fig. 2 Fig2:**
[figure not shown]
Process evaluation. Goal: to assess which intervention activities were applied and resulted in expected outputs

According to Moore et al. the process evaluation will be divided into three areas for which data will be collected [68]:1. The process of the QIC––to describe what is being applied, we will study and document the preparation phase of the QIC initiative, as well as ongoing activities throughout the cRCT, emerging changes in implementation and experiences of the intervention.2. Mechanisms of impact––to examine how the delivered QIC produced change at the intervention clinics, we will document the evidence-based changes tested, and evaluate their impact on women’s choices, as well as identify what components work and how, including the immigrant women’s contribution in coproducing the contraceptive services.3. Context–– to examine how the context affects the QIC’s implementation and outcomes, we will document how this varies across contexts, and how the intervention is delivered in the various county councils and MHCs. We will also evaluate social processes and different organizational circumstances that enable QICs as well as the target-population’s involvement.

### Quantitative data collection and analysis

To assess fidelity (quality) and dose of codesigned contraceptive services delivered (quantity), a survey will be used at each LS (every third month) that collects data on components of the intervention which have been tested at each MHC. Midwives will also be asked to complete a questionnaire regarding their experiences of evidence-based changes tested at the MHCs. To assess mechanisms of impact, the participating midwives will be asked to fill in a questionnaire on their competence and confidence in providing contraceptive counselling before and after the intervention. Additional data might also be collected as the project will use an emerging design (Table 1).

